# METFORMIN: an efficacy, safety and pharmacokinetic study on the short-term and long-term use in obese children and adolescents – study protocol of a randomized controlled study

**DOI:** 10.1186/1745-6215-15-207

**Published:** 2014-06-05

**Keywords:** Efficacy, Insulin resistance, Metformin, Paediatric obesity, Pharmacokinetics, Safety

## Abstract

**Background:**

The prevalence of childhood obesity and insulin resistance is rising, increasing the risk of diabetes mellitus type 2. To prevent these complications, lifestyle intervention is the corner stone in treatment. However, long-term efficacy of lifestyle intervention is questionable. In addition to lifestyle intervention, pharmacological treatments have been explored. Metformin has been shown to be moderately effective to reduce BMI in obese adolescents with hyperinsulinemia. However, data on pharmacokinetics and long-term efficacy and safety are lacking as well as an evidence-based dosing regimen for this age group. The primary objective of the METFORMIN study is to determine the effect of adding metformin treatment to lifestyle intervention in reducing BMI in obese adolescents with insulin resistance. In addition, the pharmacokinetics of metformin in obese adolescents will be studied.

**Methods/design:**

The METFORMIN study is a multi-centre prospective study that consists of two 18-month phases: a double-blind randomized placebo-controlled trial (part 1) and an open-label follow-up study (part 2). During part 1, the participants will be given metformin 1,000 mg or placebo twice daily and will be offered a lifestyle intervention programme; 144 participants will be included, 72 in each arm. Primary endpoints are reduction in body mass index, insulin resistance, and percentage body fat.

**Discussion:**

This study will provide data on short- and long-term efficacy and safety of metformin and on the pharmacokinetics of metformin in obese adolescents.

**Trial registration:**

ClinicalTrials.gov number
NCT01487993; EudraCT nr. 2010-023980-17. Registration date: 06-01-2011

## Background

The prevalence of obesity in adolescents is increasing rapidly, having a significant impact on both physical and psychosocial health
[1]. Currently, the worldwide prevalence of obesity in children and adolescents is 2% to 3%, using the International Obesity Taskforce standard definition for paediatric obesity in children and adolescents 5 to 17 years of age
[2]. In the Netherlands, the prevalence of obesity in children and adolescents (4–15 years) of Dutch descent is 1.8% in boys and 2.2% in girls. In Turkish boys and girls, these numbers are higher, 8.4% and 8.0%, respectively
[3].

In obese children and adolescents, insulin resistance, impaired fasting glucose, impaired glucose tolerance, dyslipidaemia, and hypertension occur with increased frequency
[4-6]. In addition, several medical conditions, such as poor pulmonary function, hepatic steatosis, sleep apnoea, and orthopaedic complications, are associated with obesity
[1,5,7,8]. These medical conditions often persist into adulthood and will result in substantial psychosocial and somatic morbidity, with loss of school or working days
[9].

Current treatments for obesity are lifestyle, drug, and surgical interventions
[10-12]. Behavioural lifestyle intervention can produce significant reduction of obesity in children and adolescents
[13]. However, the efficacy of lifestyle intervention programs on body mass index (BMI) and all related complications on the long-term are questionable, taking into account the high drop out and the frequent relapse of obesity in this group of patients. Therefore, in clinical practice, adding a pharmacological agent to conventional treatment is often considered. Three agents have been studied: orlistat, a gastrointestinal lipase inhibitor, sibutramine, a serotonin and noradrenalin re-uptake inhibitor, and metformin, an insulin sensitizing agent
[10-12,14]. Both orlistat and sibutramine have been shown to have an additional reducing effect on the absolute BMI in children and adolescents, yet medication-related adverse effects, such as tachycardia, hypertension, arrhythmia, and gastro-intestinal tract symptoms, were frequently reported
[11,15,16]. Efficacy of metformin was investigated in hyperinsulinemic, obese adolescents by Park et al. in a systematic review
[12]; they concluded that metformin is moderately efficacious in reducing BMI and insulin resistance in the short term (less than 6 months). The authors stated that large long-term studies are needed to establish the role of metformin in the treatment of obese adolescents. This conclusion is based on studies in obese adults without Type 2 diabetes mellitus (T2DM), in which metformin has been shown to prevent progression from impaired fasting glucose and impaired glucose tolerance to T2DM
[17,18]. Although results in obese children and adolescents are sparse, these results, and the observed benefits in adults, have led to increased off-label use of metformin in obese children and adolescents with, and even without insulin resistance
[19-26].

In conclusion, obesity in adolescence is increasing rapidly, with large medical and psychosocial sequelae. While standard treatment is lifestyle intervention, metformin is often added to this treatment, despite the lack of proper randomised trials on efficacy and safety, particularly upon prolonged treatment
[12,27-31]. While metformin is licensed in adolescents for the treatment of T2DM, it is not yet licensed for obese children with and without insulin resistance.

## Methods/design

### Objectives

This study has four main objectives:

The primary objective of the METFORMIN study is to determine the efficacy of metformin in combination with lifestyle intervention in obese adolescents with insulin resistance versus placebo with lifestyle intervention after 18 months in reducing BMI and insulin resistance. The secondary objective is to determine the safety and tolerability of metformin in obese adolescents with insulin resistance. The tertiary objective is to study the population pharmacokinetics (PK) of metformin in obese adolescents. Finally, the quaternary objective is to determine the long-term (36 months) efficacy and long-term safety and tolerability of metformin in obese adolescents with insulin resistance.

Other objectives are to compare values of body fat measured using bio-impedance with values of body fat measured using dual energy X-ray absorptiometry (DEXA scan), and to compare insulin sensitivity measured by the Whole Body Insulin Sensitivity Index with insulin sensitivity calculated by Homeostasis Model Assessment for Insulin Resistance (HOMA-IR) in obese children and adolescents. Furthermore, arterial stiffness will be measured and evaluated over time.

### Design

The metformin study is a multicentre study, divided in two parts, both of 18 months. The first part is a randomized, double-blind placebo controlled trial, with two parallel groups. At study entry, participants are randomized to metformin or placebo for 18 months. All participants will be offered a lifestyle intervention program. This program consists of supervised physical training twice weekly, and individual dietary advice during hospital visits. Participants will visit the hospital 9 times during this part of the study. Between these visits, monthly telephone calls are made.The second part of the study is an open label, follow-up study. Participants who remain obese and insulin-resistant at entrance of the second part, can choose between metformin treatment and no medication. Participants who do not meet these criteria, do not use medication in this part of the study. Therefore, after the follow-up study there are four arms: participants with metformin in both parts, metformin in part 1 and no medication in part 2, placebo in part 1 and metformin in part 2, and placebo in part 1 and no medication in part 2 (Figure 
1).

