### Participants

Recruitment of participants takes place at the paediatric outpatient clinics of the study centres. Patients are eligible for this study if they meet the inclusion and exclusion criteria as listed in Table 
1. Informed consent will be obtained from all participants/parents or caretakers.

**Table 1 T1:** Inclusion and exclusion criteria

**Inclusion criteria**	**Exclusion criteria**
Age: 10–16 years	Presence of T2DM, polycystic ovarian syndrome, or endocrine disorders treated with corticosteroids
Obesity defined as BMI standard deviation score >2.3	Height <-1.3 SD of target height
Insulin resistance defined as HOMA-IR ≥3.4	Syndromal disorders with or without mental retardation
Caucasian descent	Pregnancy
Informed consent signed by parents and participant	Use of anti-hyperglycaemic drugs, ritonavir or ACE-inhibitors
	(History of) alcohol abuse
	Impaired renal or hepatic function (renal function defined as glomerular filtration rate (GFR) <80 ml/min; GFR = 40 × length (cm)/serum creatinine (μmol/l); hepatic function: alanine aminotransferase >150% of normal value for age)
	Insufficient knowledge of Dutch language

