### Efficacy of metformin

To assess the effect of metformin versus placebo, the Students T test will be used to compare means of normally distributed data and the Mann-Whitney U test to compare nonparametric data. The χ^2^ test will be used for dichotomous outcomes (the development of impaired fasted glucose, impaired glucose tolerance, T2DM, and the presence of micro- and macro- vascular complications versus the study groups).General linear models (analysis of repeated measures) or mixed models (if too much data is missing) will be used to determine the therapeutic effect of the drug. After part 2 of the study, comparisons will be made between the four subgroups (metformin in part 1 and part 2; metformin in part 1 and no medication in part 2; placebo in part 1 and metformin in part 2; placebo in part 1 and no medication in part 2) (Figure 
1).

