### Oral glucose tolerance test

Oral glucose tolerance tests (OGTT) will be performed at four time points. Participants will come to the hospital after an overnight fast. After insertion of a venous cannula and after obtaining the baseline blood sample (t = 0), participants will receive a solution of glucose: 1.75 g/kg body weight with a maximum of 75 g, dissolved in 200 to 300 mL of water. Blood samples will be taken for glucose and insulin concentrations at 30, 60, 90, and 120 minutes after ingestion of the glucose solution.

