### Quaternary outcome measures

Quaternary outcome parameters for long-term efficacy and long-term safety and tolerability (36 months) of metformin are similar to the primary and secondary outcome measures. In addition, the percentage of patients that has developed impaired fasting glucose, impaired glucose tolerance, and T2DM is evaluated. Furthermore, the development of micro- and macro-vascular complications is assessed, by measuring micro-albuminuria and arterial stiffness.

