### Limitations of the study

The major limitation of our study is in the open-label, second part of the study. In this part, participants who are still eligible for receiving metformin, i.e., who remain insulin resistant and obese, may choose between taking the drug or not. This will provide a bias in the second part of the study, as participants motivated to lose weight are more likely to choose metformin compared to non-motivated participants. Possibly, this will cause an overestimation of the efficacy of metformin during the second part off the study. This will be taken into account when analysing the results of the second part of the study. The open label construction will not influence adverse reactions to the drug, therefore making it possible to draw firm conclusions about the 36-month safety and tolerability of metformin.

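### Part 2 medication appears to be restricted by the week 73 HOMA-IR, and HOMA-IR is then compared between the groups so formed, so selection on the outcome and regression to the mean distort the part 2 comparison

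*Protocol article*

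**What the plan says.** Under Design, the protocol article sets who may take metformin in part 2: "Participants who remain obese and insulin-resistant at entrance of the second part, can choose between metformin treatment and no medication". For everyone else: "Participants who do not meet these criteria, do not use medication in this part of the study". The no-medication arms therefore hold two kinds of participant: those who could have had metformin and declined, and those no longer eligible.

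Insulin resistance is defined once, in Table 1, as an entry criterion: "Insulin resistance defined as HOMA-IR ≥3.4". On sampling, "Oral glucose tolerance tests (OGTT) will be performed at four time points"; Table 3 places these at weeks 0, 37, 73 and 146. Week 73 is the sample at the boundary between the parts. Week 61 has a fasting glucose and insulin pair, and the next blood sample after week 73 is at week 98.

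The analysis section says: "After part 2 of the study, comparisons will be made between the four subgroups". HOMA-IR is one of the outcomes compared, because it is a primary endpoint and "Quaternary outcome parameters for long-term efficacy and long-term safety and tolerability (36 months) of metformin are similar to the primary and secondary outcome measures". Limitations of the study repeats the eligibility rule ("participants who are still eligible for receiving metformin, i.e., who remain insulin resistant and obese, may choose between taking the drug or not") and gives one source of bias in part 2: "participants motivated to lose weight are more likely to choose metformin compared to non-motivated participants".

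**The concern.** The variable that helps decide who can be in a metformin group in part 2 is also an outcome compared between those groups. Every part 2 metformin user has been selected for a high week 73 HOMA-IR. Every participant with a low one is in a no-medication arm.

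A single HOMA-IR reading varies from visit to visit. Someone selected for a high reading tends to read lower next time, and someone selected for a low reading tends to read higher. Change measured from week 73 therefore falls among metformin users and rises in the no-medication arms even if the drug does nothing. The no-medication arms also contain the participants with truly lower values, so a comparison of week 146 levels, or of change from week 0, is distorted the other way.

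The HOMA-IR half of the 36-month efficacy objective is at stake. The stated limitation concerns motivated choice. It does not cover this mechanism, which would operate even if eligible participants chose at random.

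**Working it through.** **What the documents give.** Entry cut-off 3.4 (Table 1). HOMA-IR design difference 1.6 with 60 per group at a 0.05 significance level (Sample size). The article gives no misclassification rate, so there is no figure of its own on this point to reproduce. Its 144 total does follow: 60 × 1.2 = 72 per arm, and 2 × 72 = 144.

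**What they do not give, and is assumed.**
- Within-person CV of one reading: 15-40%.
- Clinic median HOMA-IR: 3.4-6.0, lognormal, between-person log-SD 0.45.
- Half of the eligible participants choose metformin, at random.
- No true change and no drug effect. Visit errors are independent unless stated otherwise.
- Only the HOMA-IR part of the eligibility rule is modelled.

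**Step 1: share reading below 3.4 at week 73.** Simulation of 1,000,000 persons per scenario, each enrolled if the entry reading is at least 3.4:

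| Clinic median | CV 15% | CV 20% | CV 30% | CV 40% |
|---|---|---|---|---|
| 3.4 | 14% | 18% | 25% | 31% |
| 4.5 | 8% | 11% | 16% | 20% |
| 6.0 | 4% | 5% | 8% | 11% |

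A wider grid (median 2.5-6.0, log-SD 0.3-0.7, CV 10-50%) was restricted to scenarios with an entry SD of 2.5-3.3; there the share is 2-44%. That SD band lies around the value implied by the sample size if a two-sided t test is assumed: 1.6/0.516 = 3.10 at 80% power and 1.6/0.597 = 2.68 at 90% power. The article states neither power nor SD for HOMA-IR, so this is only a rough anchor.

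**Step 2: how many of these are mislabelled.** At median 3.4 and CV 30%, 25.2% read below 3.4, but only 12.6% of the cohort do so with a true value of at least 3.4. The other 25.2 - 12.6 = 12.6% are correctly below the cut-off at week 73. For them, the entry reading was the misleading one.

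**Step 3: false difference between metformin and no medication, same scenario.** Let p = 0.252 be the share not eligible. Metformin users are 0.5 × (1 - p) = 0.374 of the cohort, and the no-medication arms are the remaining 0.626.
- Change from week 73 to week 146 is -0.314 in the eligible and +0.953 in the not eligible.
- No-medication mean = (0.374 × -0.314 + 0.252 × 0.953)/0.626 = +0.19.
- False difference = -0.314 - 0.19 = about -0.51, favouring metformin. At median 4.5 and CV 30% it is -0.37.
- From week 0, the eligible versus not-eligible gap is +0.52. Diluted in the same way: 0.52 × 0.252/0.626 = +0.21, against metformin.

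Over the CV 15-40% and median 3.4-6.0 scenarios, the false difference is roughly -0.04 to -0.84 from week 73 and +0.02 to +0.26 from week 0. On the wider grid, it is -0.02 to -1.42 from week 73, +0.01 to +0.36 from week 0, and +0.15 to +1.21 for the week 146 level.

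**Step 4: candidate remedies.**
- Eligible participants only: both sides have passed the same week 73 filter, and the artefact is within 0.03 of zero when choice is random.
- Week 61 as baseline for all four subgroups: about zero with independent visit errors, but up to -0.35 with serially correlated error, and about +0.1 to +0.16 if true values drift.

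**The case against.** The strongest reply has four parts.

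- **The rule is inferred.** The article gives no part 2 threshold, visit or number of readings, and a condensed article may leave these to the full protocol. This stands, and the point is worded accordingly. The structural problem remains for any rule that uses boundary HOMA-IR. Confirmatory readings would shrink the regression artefact but would not remove selection on the outcome.
- **The size is assumed.** This also stands. A reader might infer that a sixth to a third of unchanged participants are wrongly labelled recovered. The documents do not support that. It is one part of a 4-31% range (2-44% on the wider grid), and in the worked example about half of those below 3.4 were truly below it.
- **The direction is not fixed.** A reader might infer that part 2 is biased in favour of metformin. That holds only for change from week 73, and the article names no part 2 baseline. For a 36-month objective week 0 is at least as natural, and there the artefact is smaller and goes against metformin.
- **The comparison is already declared biased.** Part 2 is open-label and self-selected, it serves the fourth-ranked objective, and the authors say they will allow for bias. This limits the weight of the point. But the bias they name is motivation, and allowing for motivation does not deal with selection on week 73 HOMA-IR.

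A reader might also extend the point to the 18-month result. Nothing supports that: the selection takes place after the randomised comparison ends.

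**Conclusion.** The concern holds as a structural one. The planned four-subgroup HOMA-IR comparison is distorted without any drug effect, because HOMA-IR helps form the groups, and the limitations section does not name this source.

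The sign of each artefact follows from the selection; its size cannot be derived from the documents. Under the assumed inputs, the largest false difference is about 0.84/1.6 = 53% of the design difference from week 73 and 0.26/1.6 = 16% from week 0. The smallest are close to nothing (0.04/1.6 = 2.5% and 0.02/1.6 = about 1%). These figures rest on the assumed CV, HOMA-IR distribution, 50% random uptake and stable true values, and on a single week 73 reading against 3.4.

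The point merits a change to the part 2 analysis. It does not touch the primary result.

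**What to change.** Analysis and wording only:

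1. State how continuing insulin resistance is determined at the start of part 2: threshold, visit and number of readings. What that rule should be is left to the sponsor.
2. Make the main part 2 HOMA-IR comparison metformin versus no medication, within each part 1 arm, among participants eligible for metformin at week 73. Report those not eligible separately.
3. If all four subgroups are still compared, add a sensitivity analysis with the already collected week 61 HOMA-IR as baseline instead of week 73. Note that it removes the artefact fully only if visit errors are independent, and that it includes 12 weeks of part 1 treatment.
4. In Limitations of the study, add selection on week 73 HOMA-IR and regression to the mean beside motivated choice.

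The cost is fewer participants in the main part 2 comparison; no visits or samples are added. Restricting to eligible participants does not remove bias from motivated choice, so that caveat stays.

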**Figure 1 F1:**
[figure not shown]
METFORMIN study flowchart.

During part 2, no supervised physical training is offered. Participants using Metformin will visit the hospital six times, participants not using medication will have three hospital visits and three phone calls. Participants using Metformin are seen more frequently to monitor potential adverse events.

The study protocol has been approved by the Medical Ethical Committee of the St Antonius Hospital, Nieuwegein, the Netherlands. The study is registered in the Clinical Trials register (ClinicalTrials.gov number
NCT01487993).

### Participants

Recruitment of participants takes place at the paediatric outpatient clinics of the study centres. Patients are eligible for this study if they meet the inclusion and exclusion criteria as listed in Table 
1. Informed consent will be obtained from all participants/parents or caretakers.

**Table 1 T1:** Inclusion and exclusion criteria

**Inclusion criteria**	**Exclusion criteria**
Age: 10–16 years	Presence of T2DM, polycystic ovarian syndrome, or endocrine disorders treated with corticosteroids
Obesity defined as BMI standard deviation score >2.3	Height <-1.3 SD of target height
Insulin resistance defined as HOMA-IR ≥3.4	Syndromal disorders with or without mental retardation
Caucasian descent	Pregnancy
Informed consent signed by parents and participant	Use of anti-hyperglycaemic drugs, ritonavir or ACE-inhibitors
	(History of) alcohol abuse
	Impaired renal or hepatic function (renal function defined as glomerular filtration rate (GFR) <80 ml/min; GFR = 40 × length (cm)/serum creatinine (μmol/l); hepatic function: alanine aminotransferase >150% of normal value for age)
	Insufficient knowledge of Dutch language

### Sample size

A power analysis for reduction in BMI (primary endpoint) and for reduction of insulin resistance calculated by the HOMA-IR has been performed. For BMI, a sample size of 47 participants per group (metformin and placebo) is sufficient to detect a change in BMI of 2.94% with 90% power. Sample size for HOMA-IR was calculated using a simulation based on retrospective data available from our obesity out-patient clinic. Group sample sizes of 60 patients in both groups were found sufficient for the detection of a difference of 1.6 with a significance level of 0.05. To prevent inadequate power due to drop out of participants, 20% more patients will be included. This means a total amount of 144 children and adolescents have to be included in the study.

### Randomisation

Subjects will be assigned to metformin or placebo in accordance with a randomisation schedule generated by the department of Clinical Pharmacy of the St Antonius Hospital, using PASW Statistics 18.0. Randomisation will be done in blocks of 20 subjects assuring a balanced study after each 20 consecutive inclusions per research site. All research staff is blinded for treatment allocation during the time of the study. Randomisation lists will be kept under secured access in the clinical pharmacy department of both participating hospitals.

The research physician assigns included participants to consecutive study numbers, which correlate with the randomisation and medication number.

